## Introduction

Retinopathy of prematurity (ROP) is a common comorbidity associated with extreme prematurity that affects up to 64% of extremely low gestational age neonates (ELGANs) below 28 weeks of gestational age (GA) (1, 2). ROP is a condition exclusive to preterm newborns and is the leading cause of blindness in ELGANs with significant neurodevelopmental implications in the short and long term (3).

Physiologic retinal development requires a relative hypoxemic microenvironment during intrauterine growth, where the arterial partial pressure of oxygen (PaO2) ranges from 30 to 40 mmHg. However, PaO2 rapidly increases to 100 mmHg whithin minutes after premature birth, hindering retinal blood vessel growth. In the first stage of ROP, hyperoxia suppresses the production of vascular endothelial growth factor (VEGF) and erythropoietin (EPO), leading to retinal vasoconstriction and localized hypoxia, ultimately causing delayed retinal development. Additionally, preterm birth causes the depletion of factors such as insulin-like growth factor 1 (IGF-1), which seems to contribute to the alteration of retinal vascular development (4, 5). In the second stage, the prolonged retinal hypoxia triggers the production of proangiogenic factors, leading to pathological and aberrant neovascularization that leads to the formation of fibrous scars and may potentially result in retinal detachment and subsequent risk of blindness or severe loss of visual acuity.

The severity of ROP inversely correlates with the degree of prematurity (6). Prematurity creates a favorable environment for this condition by exposing the immature retina to high oxygen levels. Despite extensive research conducted over the past six decades to investigate the relationship between prematurity, oxygen, and ROP, the treatment strategies for ROP are focused on applying therapies once the pathology has been developed such as laser therapies or intravitreal injection of bevacizumab (7, 8). However, no effective strategy has been found to significantly prevent the progression of ROP before its onset. Limited supplemental oxygen has been evaluated as a potential intervention, but this practice has the counterpart of increasing mortality (9, 10).

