### Primary outcome

The primary outcome is the incidence of ROP in both groups. Diagnosis and staging of ROP will be established according to “International Classification of the Retinopathy of Prematurity, Third Edition (ICROP3)”. ROP diagnosis will be made by an expert ophthalmologist using indirect ophthalmoscopy and RetCam imaging.

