### Sample size calculation and power

We consider the development of ROP a competitive outcome with mortality due to its late onset during postnatal development. The combined variable death or ROP was considered the primary study variable. The incidence of death or ROP in our center in ≤28 weeks is 41%. A 50% reduction in the incidence will be considered clinically significant, so considering a significance level of 0.05 and a power of 0.8, the calculated sample size is 122 patients. Assuming a drop ratio of 10%, 134 patients will be recruited for the study (67 in each group).

University and Polytechnic Hospital La Fe is a tertiary center with 6,000–6,500 births annually. In addition, two other recruiting centers, University Clinical Hospital of Santiago (2,000–2,200 births annually) and Maternal and Child University Hospital Complex of Las Palmas (4,500–4,800 births annually), are included in the study, so we estimate that the sample size could be accomplished in the three years of the study duration.

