### Randomization and blinding

Randomization will be done just before birth and generated by random numbers using the R® 3.5.1 software (R Development Core Team, Auckland, New Zealand). Patient numbers will be assigned sequentially by order of entry into the study. Randomization will be stratified into two groups by gestational age (GA) (23–25 and 26–28), using block randomization. The Biostatistics Unit will provide a randomization list for the corresponding Neonatology Service containing the patient number and another for the Blood Bank Service holding the related treatment branch and the patient number. The neonatologist in charge of the patient will assign the patient a number for the study, ensuring that it has not been given to any other patient. Once the number has been provided, it will be sent to the Blood Bank, responsible for keeping the randomization list containing all the information about it.

The Blood Bank will receive the UCB from the delivery room. It will verify that it meets the quality criteria established by the Blood Bank and aliquot it into one or several units of blood, depending on the volume available. Once a transfusion is prescribed for a participating patient, the Blood Bank will dispense either UCB or RBC according to the assigned group in the same container bag typically used in the Neonatology Unit to be indistinguishable from guaranteeing the blinding. The neonatologist will remain blind to the randomization group, as will the nursing staff and specialists in charge of patient care.

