### Statistical analysis

The following sets of analyses are planned: (1) All included patients, regardless of whether they were transfused or not; (2) All included patients who received transfusions, as per intention-to-treat (including intervention group patients who received adult donor blood transfusions due to unavailability of umbilical cord blood); (3) All included patients who received transfusions as per protocol (excluding intervention group patients who received adult donor blood transfusions). Secondary analyses will also examine the effect of the two treatment strategies on the described secondary variables. An interim analysis of the results will be conducted once half of the sample has been collected to assess the presence of any relevant safety or mortality outcomes. An external committee will be proposed to perform the calculations while maintaining blinding until evaluation.

Categorical variables are described with each category's numerical count (percentage). If the application assumptions are met, they are compared with Pearson's chi-square test, and if not, Fisher's exact test. Continuous variables are represented with Tuckey box plots. If the constant variables are standard (*p* > 0.05 in the Shapiro–Wilk test), they are described with the mean ± standard deviation. They are compared using Student's *t*-test, first testing the hypothesis of equality of variances using Levene's test. If abnormal, they are described with a median (p25, p75) and compared with the nonparametric Mann–Whitney *U*-test. Comparison between both groups of repeated measures over time is performed by a two-way analysis of variance (ANOVA) test, first testing Mauchly's sphericity hypothesis and rejecting it with *p* < 0.05. Survival times are expressed with their median [95% confidence interval (95% CI)], and between-group comparison is performed with the log-rank test. Throughout the study, a *p* < 0.05 is accepted as the limit of statistical significance. The magnitude of the effect is quantified with the risk difference (expressed as a percentage), and its precision is indicated with the 95% CI.

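### Randomisation is stratified by gestational age, but the only test stated for binary outcomes ignores the strata; this loses some efficiency if gestational age is prognostic, but is not invalid

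*Protocol article*

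**What the plan says.** Under Randomization and blinding, the protocol article states: "Randomization will be stratified into two groups by gestational age (GA"), with groups of 23–25 and 26–28 weeks and allocation in blocks.

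Under Statistical analysis, tests are listed by type of variable. Categorical variables are "compared with Pearson's chi-square test, and if not, Fisher's exact test", the choice depending on whether the chi-square assumptions are met. The same section adds: "The magnitude of the effect is quantified with the risk difference (expressed as a percentage"), with a 95% confidence interval. It mentions no stratified test, stratified risk difference or model containing gestational age.

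The primary outcome is binary on either of the article's two descriptions. Primary outcome says "The primary outcome is the incidence of ROP in both groups"; Sample size calculation and power says "The combined variable death or ROP was considered the primary study variable". That conflict is a separate matter. Either way, the chi-square or Fisher test is the only one stated that fits.

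On prognosis, the Introduction says: "The severity of ROP inversely correlates with the degree of prematurity". It then describes prematurity as favouring the condition. No event rate is given for either stratum.

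**The concern.** Blocking within strata keeps the arms nearly equal in gestational-age mix, so chance imbalance on that factor no longer adds to the variability of the treatment comparison. A test that ignores the strata still counts the difference in risk between younger and older infants as random noise. If that difference is real, the standard error is overstated. The test then rejects a true null less often than 5%, the interval covers more than 95%, and some power is lost.

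What is at stake is precision that the design has already bought. It matters more here because the planned number gives less than the stated 80% power for a two-sided test at 0.05, as shown in the working. That shortfall is a separate issue and does not make this one more serious.

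**Working it through.** **Inputs from the protocol article (Sample size calculation and power; Study design).** "The incidence of death or ROP in our center in ≤28 weeks is 41" per cent. "A 50% reduction in the incidence will be considered clinically significant", so 41% falls to 20.5%. Significance level 0.05, power 0.8, 122 infants, 134 after 10% drop-out, allocation 1:1.

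**Assumed, because the documents do not give them.** The share of infants at 23–25 weeks (35–40%), the control risk in each stratum (weighted to average 41%), and a relative risk of 0.5 in both strata.

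**1. The plan's own figure.** With the pooled two-proportion formula

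n per arm = [z_α √(2p̄(1−p̄)) + z_β √(p₁(1−p₁) + p₂(1−p₂))]² / (p₁−p₂)²,

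and p₁ = 0.41, p₂ = 0.205, p̄ = 0.3075, z_β = 0.842:
- One-sided 0.05 gives 61.6, so 62 per arm or 124 in total. The arcsine version gives 61.04 per arm, about 122.
- Two-sided 0.05 gives 78.4, so 79 per arm or 158 in total.
- Drop-out: 122 × 1.10 = 134.2.

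The stated 122 therefore matches a one-sided calculation. At two-sided 0.05, power is about 69% with 61 per arm and 73% with 67 per arm.

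**2. Why the unadjusted standard error is too large.** With a share w in the younger stratum, the null variance per infant splits as

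p(1−p) = [w p₁(1−p₁) + (1−w) p₂(1−p₂)] + w(1−w)(p₁−p₂)²,

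where p₁ and p₂ are now the stratum risks. Stratified blocking removes the last term from the sampling variance, but the unadjusted test keeps it. If r is the within-stratum share of the total, the null rejection rate is approximately 2[1 − Φ(1.96/√r)]. The total is 0.41 × 0.59 = 0.2419.
- 50%/35%, w = 0.40: between-stratum term 0.24 × 0.15² = 0.0054; r = 0.978; about 4.7%.
- 65%/25%, w = 0.40: 0.24 × 0.40² = 0.0384; r = 0.841; about 3.3%.
- 75%/22.7%, w = 0.35: 0.2275 × 0.523² = 0.0622; r = 0.743; about 2.3%.

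**3. Simulation.** 200,000 trials per scenario, exact balance within strata, two-sided 0.05. Pearson is the unadjusted chi-square; CMH is Cochran-Mantel-Haenszel without continuity correction.

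| Share at 23–25 wk | Control risks | N | Null rejection, Pearson / CMH | Power, Pearson / CMH | Gain (points) |
|---|---|---|---|---|---|
| 40% | 41% / 41% | 134 | 4.6% / 4.6% | 73.8% / 73.8% | 0 |
| 40% | 50% / 35% | 134 | 4.4% / 4.8% | 74.3% / 74.6% | 0.3 |
| 40% | 50% / 35% | 122 | 5.0% / 5.1% | 69.8% / 70.3% | 0.5 |
| 35% | 65% / 28.1% | 122 | 3.8% / 4.9% | 70.2% / 73.6% | 3.4 |
| 40% | 65% / 25% | 134 | 3.0% / 5.0% | 75.5% / 78.9% | 3.4 |
| 35% | 75% / 22.7% | 122 | 2.5% / 4.9% | 70.9% / 77.6% | 6.7 |

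Because counts are discrete, these rates differ by a few tenths of a point from the approximation in step 2.

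**4. Interval width.** At N = 134, w = 0.40 and relative risk 0.5, the mean half-width of the 95% interval falls from 15.1 to 14.4 points at 60%/28%, and from 15.1 to 13.6 points at 70%/22%. The simple large-sample stratified interval covered 94.1% to 94.6%. The unadjusted interval covered 94.5% to 94.8% where the strata had equal risks.

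**5. Continuity correction.** With it, CMH power in the last three rows is 66.4%, 72.4% and 70.5%, below the planned Pearson test each time (70.2%, 75.5%, 70.9%).

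**The case against.** **The paragraph is generic and an unseen analysis plan may adjust.** It is true that the section lists tests by variable type and does not name the primary analysis. But it does state a test, the test is unstratified, and nothing else in the article suits a binary outcome. An analysis plan that stratified would depart from this text, so the wording merits correction either way.

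**The planned test is valid.** This stands. A reader might infer that ignoring the strata invalidates the comparison or inflates false positives. It does not: when gestational age is prognostic, the unadjusted test errs on the conservative side. The 5.0% to 5.3% seen for both tests at N = 122 with weak or no gradient reflects discreteness.

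**The size rests on assumed inputs.** This also stands. A reader might take gestational age as a documented strong predictor and quote only the larger gains. The Introduction's sentence concerns severity of ROP, whereas the endpoint is any ROP, or death or ROP, and no risk by stratum is given. At 50%/35% the gain is almost nil. A steeper assumption such as 80%/15% would give about 9 points at N = 134 (78.3% vs 87.4%), but nothing in the article supports choosing it.

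**Exact balance is idealised.** This stands in part. With random 10% loss, the unadjusted null rate rises from 3.0% to 3.5% at 65%/25%, and from 4.4% to 4.8% at 50%/35%. The effect shrinks but keeps its direction.

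**The remedy can backfire.** This stands for the continuity-corrected test, so the version must be named.

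**Conclusion.** The point holds as one of efficiency. The design stratifies on gestational age and the stated analysis ignores it. If gestational age is prognostic, the test is conservative and the interval too wide.

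The loss cannot be fixed from the documents. With control risks averaging 41%, a common relative risk of 0.5 and 122 to 134 infants, it runs from about 0 power points (equal risks, or 50%/35%) through about 3 (65% vs 25–28%) to about 7 (75% vs 23%). Over the unequal-risk scenarios, the unadjusted null rejection rate goes from roughly nominal (about 4.5% at 50%/35% with 134 infants) to 2.5%.

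The change should be made because it is free and fits the design, not because the planned test is wrong. It would not by itself make good the sample-size shortfall: at N = 122, the steepest case tabulated still reaches only 77.6%.

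**What to change.** - Name as the primary test the Cochran-Mantel-Haenszel test stratified by the randomised gestational-age group, **without continuity correction**.
- Report the Mantel-Haenszel (stratified) risk difference with its 95% confidence interval. This keeps the effect scale already chosen.
- Keep the unadjusted chi-square as a sensitivity analysis.
- Use the same strata for the binary secondary outcomes.
- Settle the wording before the blind is opened for analysis.

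The cost is a sentence or two of text. The stratum is recorded at randomisation, so no extra data or infants are needed. If the gradient proves weak, the uncorrected test loses essentially nothing: with equal risks its power matched the Pearson test (73.8% for both at N = 134).

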## Appendix II

(1) Retinopathy biomarkers
  - VEGF: VEGF or VEGF-A will be determined weekly during the first six weeks of life. The blood will be collected and centrifuged to separate the serum. It will be stored at −80°C until processed with Human VEGF Quantikine ELISA Kit.
  - EPO: It will be determined at first, 21, and 35 days of life by using Immulite 2000 system.
  - IGF-1: Using the Liason system will determine it at first, 21, and 35 days of life.
(2) Oxidative stress biomarkers in urine
  Validated methods based on liquid chromatography coupled to tandem mass spectrometry (UPLC- MSMS) will be used. Integrated functions within the PLS Toolbox (Eigenvector Research), as well as in-house written parts, will be used for data modeling and comparisons between groups, using variable reduction methods based on principal component analysis (PCA) and classification methods, such as the analysis partial least squares discriminant (PLS-DA).
(3) Blood cell typing in umbilical cord blood
  To quantify the number of hematopoietic stem cells, mesenchymal and endothelial cells in cord blood samples will be collected in an EDTA tube. The analysis will be performed by flow cytometry (BD FACScanto II (Becton Dickinson) and Diva Software (Becton Dickinson Biosciences)”. Mesenchymal cells will be tested to ensure they meet the minimum definition criteria, including the culture of mesenchymal cells for this purpose.

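### A Shapiro-Wilk p-value from the trial data decides which summary and which test each secondary continuous outcome gets, and the only effect measure named does not apply to these outcomes

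*Protocol article*

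**What the plan says.** The protocol article's Statistical analysis section fixes a two-stage rule for continuous variables.

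- **Normality passed.** Variables with p > 0.05 "in the Shapiro–Wilk test), they are described with the mean ± standard deviation" and compared with Student's t-test, "first testing the hypothesis of equality of variances using" Levene's test. The text gives no action for the case where Levene's test rejects.
- **Normality rejected.** "If abnormal, they are described with a median (p25, p75) and compared with the nonparametric" Mann-Whitney test.
- **Repeated measures.** "Comparison between both groups of repeated measures over time is performed by a two-way analysis of variance (ANOVA) test", after a Mauchly test of sphericity.
- **Effect size.** The section quantifies the effect by the risk difference with its 95% CI and names no measure for continuous outcomes.

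Appendix II gives the biomarker schedule. For VEGF: "VEGF or VEGF-A will be determined weekly during the first six weeks of life". For EPO: "It will be determined at first, 21, and 35 days of life by using Immulite 2000 system"; IGF-1 follows the same three days. The primary endpoint is binary: "The primary outcome is the incidence of ROP in both groups".

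**The concern.** The t-test asks whether two means differ. Mann-Whitney asks whether one distribution tends to lie above the other. Under this rule a p-value that carries no information about treatment decides which of the two questions the trial answers. Nobody can say beforehand what the comparison of, say, transfusion volume will estimate.

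At stake is the trial's supporting evidence: VEGF, EPO, IGF-1, HbF, haematocrit and haemoglobin, and transfusion number and volume. If a biomarker is shown as means at some visits and medians at others, its course cannot be read as one series or combined with other studies. With the risk difference as the only named measure, these outcomes may end with p-values and no estimate of how large the difference is.

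**Working it through.** **Inputs from the article.** The Shapiro-Wilk threshold is 0.05, Levene's test precedes the t-test, and Mann-Whitney is the alternative (Statistical analysis). VEGF has 6 visits, EPO and IGF-1 have 3 (Appendix II). An arm size of 61 is 122/2 (Sample size calculation and power). The plan has no figure of its own for continuous outcomes; the 122 was derived for a binary outcome and supplies only the arm size.

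**Assumptions, because the article gives no values.** Distributions, SDs, within-infant correlation (0 or 0.7), smaller or unequal arms, and Welch's test whenever Levene rejects. The article does not say whether Shapiro-Wilk is applied per arm or to the pooled data, so both are shown where possible.

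**Step 1: how often a biomarker changes summary between visits.** Let q be the chance that one visit goes to the means branch. With k independent visits,

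P(mixture) = 1 − q^k − (1 − q)^k.

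For truly normal data, q = 0.95² = 0.9025 if each arm must pass, and 0.95 if the data are pooled.

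- VEGF, k = 6, per arm: 1 − 0.9025⁶ − 0.0975⁶ = 1 − 0.540 − 0.000 = 0.46. Pooled: 1 − 0.95⁶ − 0.05⁶ = 1 − 0.735 − 0.000 = 0.26.
- EPO and IGF-1, k = 3, per arm: 1 − 0.735 − 0.001 = 0.26. Pooled: 1 − 0.857 − 0.000 = 0.14.

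Simulation of the six-visit case with normal data, per arm, gives 44% (30 per arm) and 46% (61 per arm), in agreement. For log-normal data over six visits (1500 runs per setting, range over correlation 0 and 0.7):

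| log-SD | 30 per arm | 61 per arm |
|---|---|---|
| 0.2 | 82-91% | 84-96% |
| 0.3 | 84-95% | 42-50% |
| 0.4 | 63-75% | 8-10% |
| 0.5 | 33-38% | under 1% |
| 0.8 | about 1% | 0% |

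Switching is common for normal or mildly skewed data. It fades under strong skew, because the median is then chosen at every visit.

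**Step 2: type I error of the whole rule at nominal 0.05.** It is a weighted sum, R = q·r(t) + (1 − q)·r(MW), where r is the rejection rate within each branch. With 5000 runs per setting the Monte Carlo standard error is √(0.05 × 0.95/5000) = 0.003.

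| Setting | Rule | Welch alone |
|---|---|---|
| Same distribution in both arms, 15 to 61 per arm | 4.3-5.4% | near 5% |
| Normal, SD ratio 2, 61 vs 61 | 5.2-5.5% | 5.2-5.3% |
| Normal, SD ratio 2, larger SD in smaller arm, 40 vs 61 or 20 vs 40 | 5.9-6.6% | 4.7-5.4% |

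Two settings show how the sum behaves.

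- 40 vs 61, normality tested per arm: 0.893 × 0.054 + 0.107 × 0.142 = 0.048 + 0.015 = 0.063. The excess comes from the Mann-Whitney branch.
- Exponential data, 15 per arm, per arm: 0.099 × 0.121 + 0.901 × 0.041 = 0.012 + 0.037 = 0.049. The t-test branch alone rejects in 12%, but it is rarely entered and the overall rate is nominal.

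Analysis set 3 removes only intervention infants who received adult blood, and the Discussion expects allogeneic supplements to be usual, so that set could well be unbalanced. At an assumed 60 vs 25 with the larger SD in the smaller arm (ratios 1.3 to 2), simulations give 5.9-7.2% for the rule and 4.5-5.2% for Welch. With the larger SD in the larger arm the rule gives 4.3-4.5%; with equal SDs it gives 4.5%.

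**Step 3: effect estimate.** The named measure, a risk difference, needs a binary outcome. A t-test would lead to a mean difference and Mann-Whitney to a shift or a probability. The article names neither, and the rule would make the choice depend on the data.

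**The case against.** The strongest case against is that the practical harm is small, and much of that stands.

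- **Weekly tests.** A reader might infer that the six VEGF measurements would be compared by a mixture of t-tests and Mann-Whitney tests. The article does not support this: it sends the between-group comparison of repeated measures to two-way ANOVA. The switching concerns the summaries at each visit and any comparison at a single time point.
- **Error control.** A reader might infer that type I error is out of control. Step 2 shows that it is not. The excess needs unequal arms and unequal SDs in one particular direction, and the reverse direction is slightly conservative. In set 3, exclusion after randomisation is a larger problem than one or two points of alpha.
- **Skewed data with equal means.** Simulations with equal means and unequal spread show the rule rejecting in 18-24% of trials against 5-6% for Welch. This is not a false-positive rate for Mann-Whitney, because the two distributions really differ. It is an error only if the mean is the target, and the article never says that it is. It illustrates the unsettled question, not a loss of error control.
- **Levene's test.** It chooses no summary; only Shapiro-Wilk does.
- **Left to the analysis plan.** Scales and models per outcome are often set out there, and that document is not shown. But the article is not silent: it states the two-stage rule and one effect measure, and an analysis plan that follows it would inherit both.

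What remains after these concessions is the data-driven choice of summary, test and target.

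**Conclusion.** The point holds as a modest improvement to the secondary continuous outcomes. The stated rule leaves the summary, the test and the quantity compared open until the data are seen, and the only named effect measure cannot be used for these outcomes.

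For a six-visit biomarker with normal data, a mixture of means and medians is expected in roughly a quarter (pooled test) to nearly a half (per-arm test) of trials. With log-normal data it ranges from over 90% to nil, depending on skew and arm size. Type I error is near 5% in most settings and about 6-7% in the one unfavourable combination. All of these figures rest on assumed distributions, SDs and group sizes. The primary outcome comparison and the repeated-measures ANOVA are not affected.

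**What to change.** Delete the Shapiro-Wilk and Levene pre-tests. State for each continuous outcome one scale, one summary and one method, used at every visit and in every analysis set. For example:

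- VEGF, EPO, IGF-1 and other assays expected to be skewed: log scale, Welch's t-test or a linear model, reported as a ratio with its 95% CI.
- Haematocrit, haemoglobin and HbF: original scale, Welch's t-test or a linear model, reported as a mean difference with its 95% CI.
- Number and volume of transfusions: Mann-Whitney with a Hodges-Lehmann difference and its 95% CI.

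Keep the risk difference for binary outcomes and say that it applies to those only. The cost is wording and a slight loss of efficiency where variances are truly equal; conduct, data collection and sample size do not change. The change should be dated before the blind is opened.

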### Secondary outcomes

Outcomes related to effectiveness
-Recovery of hematocrit and hemoglobin values.-Transfusion requirements during admission (number and volume of transfusions received).-Treatment with EPO and other adjuvant treatments for anemia such as iron and folic acid supplementation (time of initiation, number of doses received).-Assessment of post-transfusion tissue oxygen transfer status: Brain and somatic NIRS value, oxygen saturation measured by pulse oximetry, lactate, HbF levels.Outcomes related to safety
-Incidence of acute transfusion reactions.-Incidence of late complications: bronchopulmonary dysplasia, periventricular leukomalacia, necrotizing enterocolitis, hemodynamically significant patent ductus arteriosus, sepsis, and death.Outcomes related to retinopathy markers
-Serum levels of EPO, VEGF and IGF-1.-HbF levels.Outcomes related to ROP treatment
-ROP severity-Laser therapy-Anti-VEGF administrationOutcomes related to UCB cellularity and oxidative stress.
-Quantification of reactive oxygen species in urine.-Composition of stem cells in UCB.

Data concerning retinopathy and oxidative stress biomarkers quantification and stem cells typification is provided in Appendix II.

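### Serial EPO, VEGF and IGF-1 are to be compared by classical repeated-measures ANOVA, which in standard form discards every infant who dies or misses a draw

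*Protocol article*

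**What the plan says.** The Statistical analysis section names one procedure for all serial data: "Comparison between both groups of repeated measures over time is performed by a two-way analysis of variance (ANOVA) test". Before it comes a Mauchly check of sphericity at the 5% level. The section mentions no other model for repeated measures.

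The data this applies to include the markers listed under Secondary outcomes as "Serum levels of EPO, VEGF and IGF-1". Appendix II gives their schedules:
- VEGF: "VEGF or VEGF-A will be determined weekly during the first six weeks of life", so about six draws.
- EPO: "It will be determined at first, 21, and 35 days of life by using Immulite 2000 system", so three draws.
- IGF-1: "Using the Liason system will determine it at first, 21, and 35 days of life", so three draws.

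The protocol expects deaths. Secondary outcomes lists death among the late complications, and the sample size section says: "We consider the development of ROP a competitive outcome with mortality".

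**The concern.** Mauchly's test has a use only in the classical within-subject ANOVA, so the wording fixes that form. In its standard form each infant must have a complete set of values. One who dies in week four, or misses a single VEGF draw, is lost from the whole comparison, including the samples already taken and assayed.

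Two things follow. Precision falls, because valid data are thrown away. The infants who remain are also selected by events after randomization: they survived and were fully sampled, and those who died are always among the excluded. The article's Discussion hopes to study ROP mechanisms and perhaps build a predictive model from these markers, so the selection matters to the mechanistic reading of the trial.

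A smaller matter is the first-day EPO and IGF-1 value. It enters as one more level of the time factor and not as a covariate, although transfusion may have had little or no time to act on it. That dilutes the group main effect.

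**Working it through.** The document gives no figure for the biomarker comparison, so there is none to reproduce. The check asks how many infants a complete-data method would keep, and what the handling of the first-day value costs.

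**Inputs from the document.** 134 infants, 67 per arm (sample size section); K = 6 draws for VEGF and K = 3 for EPO and IGF-1 (Appendix II).

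**Assumed inputs.** m = proportion dying before the last draw, 5% to 20%. q = chance that a survivor misses any one draw, 0% to 10%, independent between draws. The document gives neither. Its 41% is death or ROP combined and cannot serve as a death rate.

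**Infants with complete data** = 134 × (1 − m) × (1 − q)^K.

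| Assumed m, q | EPO, IGF-1 (K = 3) | VEGF (K = 6) |
|---|---|---|
| 5%, 0% | 134 × 0.95 = 127 | 134 × 0.95 = 127 |
| 10%, 5% | 134 × 0.90 × 0.857 = 103 | 134 × 0.90 × 0.735 = 89 |
| 20%, 10% | 134 × 0.80 × 0.729 = 78 | 134 × 0.80 × 0.531 = 57 |

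The loss is 7 to 56 infants (5% to 42%) for EPO and IGF-1, and 7 to 77 (5% to 57%) for VEGF.

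**First-day value (EPO and IGF-1).** This was a simulation with draws on days 1, 21 and 35, equal correlation ρ between draws, an assumed effect of 0.4 SD on days 21 and 35 and none on day 1, and two-sided α = 0.05. It compares the two ANOVA tests with an analysis of covariance (ANCOVA) of the mean later value on the first-day value.

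| Infants per arm | ρ | ANOVA group main effect | ANOVA group-by-time | ANCOVA |
|---|---|---|---|---|
| 67 | 0.3 | 56% | 51% | 86% |
| 67 | 0.5 | 47% | 65% | 91% |
| 67 | 0.7 | 39% | 89% | 97% |
| 50 | 0.3 | 44% | 39% | 74% |
| 50 | 0.5 | 36% | 54% | 79% |
| 50 | 0.7 | 32% | 76% | 91% |

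Fifty per arm is close to the middle scenario above (103 / 2 = 51.5).

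Hand check at ρ = 0.5 with 67 per arm:
- Main effect: the difference averaged over three draws is 0.4 × 2/3 = 0.267. The variance of an infant's mean is (1 + 2 × 0.5)/3 = 0.667, so the standard error is √(2 × 0.667/67) = 0.141. The ratio is 1.89, giving power of about 47%.
- ANCOVA: the variance of the mean of two later draws is (1 + 0.5)/2 = 0.75. Removing the part explained by day 1 (0.5² = 0.25) leaves 0.50, so the standard error is √(2 × 0.50/67) = 0.122. The ratio is 0.4/0.122 = 3.27, giving power of about 91%.

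With no true effect and complete data, the rejection rates of the three tests lay between 4.5% and 6.5% over 2,000 simulated trials per setting, that is, near 5%. The first-day point therefore concerns efficiency, not type I error.

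**The case against.** The strongest case against has five parts.

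- **No exclusion rule is written.** The article nowhere says that infants with a missing draw are dropped. That is true: the exclusion follows from the method named. But the method is stated outright, so this is more than a detail left to a fuller document.
- **The size is all assumption.** This also stands. Missed draws are likely to cluster within infants, which would leave more complete cases at the same rate per draw. Not every death need precede the last draw. That infants who miss draws are sicker is plausible but undocumented. The direction does not depend on the rates; the size does.
- **The first-day value is not ignored.** A reader might infer that the ANOVA throws the baseline away. It does not: the value is a level of the time factor, and the group-by-time test uses it. Nor is a clean baseline established for every marker. No first-day VEGF draw is named, randomization comes just before birth, so every postnatal draw follows it, and nothing says the first-day draw precedes the first transfusion.
- **The missing step after Mauchly's test.** A reader might count it as an error that no action is given when sphericity is rejected. A standard correction is the kind of detail an article may leave to the full protocol or analysis plan, so it is not held against the plan.
- **A mixed model does not solve death.** Correct. A likelihood-based model implicitly carries trajectories past death, so its estimates cannot simply be labelled as applying to infants alive at each time. Its gain is narrower: it recovers the samples taken before death and around missed draws.

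**Conclusion.** The point holds in limited form. The article fixes a complete-data method for serial samples in a population where it expects deaths, and a better method is available at almost no cost. Under the assumed rates, the ANOVA would keep between 127 and 57 of 134 infants for VEGF and between 127 and 78 for EPO and IGF-1. At the mild end of that range little is lost.

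Using first-day EPO and IGF-1 as outcome levels lowered power at every correlation tried (0.3 to 0.7), given an assumed constant effect of 0.4 SD on the later days. The gap to the group-by-time test narrows as the correlation rises (89% against 97% at 0.7 with 67 per arm).

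The documents do not support reading this as a false-positive problem, or as a threat to the primary comparison or the sample size. Only secondary outcomes are touched, so priority is low.

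**What to change.** In the Statistical analysis section, replace the two-way ANOVA and the Mauchly step with a linear mixed model for repeated measures:
- use all available draws;
- include group, time as a factor, group-by-time and the gestational-age randomization stratum, with unstructured covariance;
- for EPO and IGF-1 only, add the first-day value as a covariate where it was drawn before the first transfusion, and model days 21 and 35 as outcomes. State how infants without such a value are handled, so that the complete-case loss does not return by that route.

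State that the model assumes missing at random for missed draws and that it implicitly extrapolates beyond death. Report deaths by arm beside the marker results, with a sensitivity analysis among infants alive at each time point.

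The cost is a change of analysis wording and modest programming; no new data or samples are needed. The price is the missing-at-random assumption, which cannot be verified from the data.
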